### 3.1.5 Preoperative RCRI+age, combined with MINS

For the purpose of the study, and to reflect the current practice, MINS will be defined as any elevated troponin (higher than the local lab threshold) judged to be due to myocardial ischemia (i.e. without evidence of a non-ischemic etiology [e.g. chronic elevation, pulmonary embolism {PE}, sepsis, cardioversion]) that occurred within the first 28 days after the initiation of surgery. *The only exceptions to the definition of an elevated troponin will be to use a higher threshold for troponin T (TnT) of  $\geq 30$  ng/L, and for high-sensitivity troponin T (hsTnT) of 20 to  $< 65$  ng/L with an absolute change of at least 5 ng/L or an hsTnT level  $\geq 65$  ng/L. These threshold for TnT and hsTnT are based upon data from a large international prospective perioperative cohort study that established troponin thresholds that were independently associated with 30-day mortality after noncardiac surgery.* The occurrence of MINS according to this definition, as a predictor/exposure, will be based on the in-hospital postoperative troponin measurement, and on any other troponin measurement occurring within the 28 days after surgery. For the primary research question, patients will be considered as meeting the MINS definition regardless of whether this meets the universal definition of myocardial infarction.

For the purpose of the primary research questions, study participants will be assigned to the high-risk category (i.e., ‘exposed’) when they are at high risk as per the preoperative RCRI+age assessment

and they experience MINS; and to the low-risk category (i.e., not ‘exposed’), if they are at high risk as per the preoperative RCRI+age assessment but they do not experience MINS, or if they are at low risk as per the preoperative RCRI+age assessment.

### **3.2 Risk to the Safety of Patients**

It is unlikely that there are risks associated with completing the frailty assessments via the FP and CFS tools. The risk of loss of confidentiality to study participants is minimal, as all the electronic data will be deidentified, and will be stored in password-protected files in password-protected computers. The study key will be locked in cabinet, in a locked office.

Potential benefits include early recognition of lower functional status and frailty, which may not otherwise have been detected through routine preoperative assessment. This could prompt early intervention (for example, a referral to a physiotherapist and/or dietician prior to surgery).

## **4. STUDY OUTCOMES**

The predictive performance of perioperative frailty and cardiovascular risk assessments will be assessed upon the following clinical outcomes.

### **4.1 Primary clinical outcomes**

The primary outcome is all-cause death or new disability at 6 months after surgery. We will measure disability in several domains (including cognition, mobility, self-care, participation) using the 12-item World Health Organization Disability Assessment Schedule (WHODAS 2.0), a patient-reported outcome tool widely validated in surgical older populations. New disability will be defined as a disability score  $\geq 25\%$  at follow-up, or a score increase of  $\geq 8\%$  for those already disabled at baseline.

### **4.2 Secondary clinical outcomes**

Secondary outcomes include:

- all cause death or new disability at 28 days and at 1 year after surgery;
- all cause death at 28 days, 6 months, and 1 year after surgery;
- disability at 28 days, 6 months, and 1 year after surgery;
- oncologic outcomes, including progression-free survival (PFS) and cancer-specific death, up to 1 year after surgery;
- major vascular complications (at 28 days, 6 months, and 1 year after surgery) defined as a composite of vascular death, and non-fatal myocardial infarction (or myocardial injury for the 28-day time point), stroke, symptomatic proximal venous thromboembolism, and cardiac arrest;
- infection, and infection with sepsis (at 28 days, 6 months, and 1 year after surgery);
- unplanned admission to ICU;
- length of stay;
- in-hospital delirium;
- postoperative cognitive changes at 6 months and at 1 year based on MoCA;
- chemotherapy-related outcomes, which include: tolerance as objectively defined by total dose received and time to completion; patient’s decisional regret (i.e., distress or remorse after a health

care decision, i.e., to undergo chemotherapy); change in health-related function or well-being (WHODAS 2.0); and change in cognitive performance (MoCA).

Appendix II includes the study clinical outcome definitions.

### **4.3 Feasibility and acceptability outcomes**

The feasibility of frailty assessment will be defined based on the average time and rate of completion of the FP and CFS (and sub-items of the FP). Acceptance of frailty assessment according to physicians will be defined based on ease of use and clinical relevance, according to relevant items of the OADRI. Patient's acceptability of frailty assessments will be measured administering a brief exit questionnaire. Appendix III includes details on how acceptability of frailty instruments from physicians' and patients' perspective will be measured in the study.

### **4.4 Adjudication of study outcomes**

The Event Adjudication Committee consists of clinicians with expertise in perioperative outcomes who are blinded to treatment allocation and who will oversee the adjudication of the following outcomes: MINS and MI. We will use the decisions of the adjudication process for all statistical analyses of these events. An event adjudication plan will be developed and govern all details, definitions, and processes of this committee.

### **4.5 Minimizing bias**

In order to reduce the influence from the knowledge of the participant frailty status (predictor) on the evaluation of disability (outcome), WHODAS 2.0 will be administered by different study personnel from those who administered the frailty assessments. In this way, they will be able to be blinded to the patient RCRI.

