| Follow-up            | 
Follow-up visits will be done (either by phone or in person) at 28 days, 6 months, and 1-year post-surgery. Efforts will be made to perform these visits in concomitance with clinical follow-ups. Frailty assessments will be repeated at the
                                                                                                                                                                                                                                                                                                                                                                                                                                                                                                                                                                                                                                                                                                                                                                                                                                                                                                                                                                                                                                                                                                                 |

|  |                                                                                                                                                                                                                               |
|--|-------------------------------------------------------------------------------------------------------------------------------------------------------------------------------------------------------------------------------|
|  | 28-day visit. WHODAS 2.0 will be administered at the 28-day, 6-month and 1-year visits. MoCA will be administered at the 6-month and 1-year visits. Study personnel will evaluate all study outcomes at each follow-up visit. |
|--|-------------------------------------------------------------------------------------------------------------------------------------------------------------------------------------------------------------------------------|

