## **5. FOLLOW UP**

### **5.1 Overall study**

Figure 2 shows the study participant timeline.

At baseline (i.e. before surgery, or before NACT for some cases), trained research personnel will collect relevant data about participant demographics, clinical and social history; will administer the WHODAS 2.0 questionnaire and the MoCA; and will assess for frailty. A trained clinical research assistant will measure frailty, first based on the CFS, and then administering the FP tests/questions. In patients undergoing NACT, the study personnel will repeat the frailty, WHODAS 2.0, and MoCA assessments before surgery, after the NACT is deemed to be terminated.

Study personnel will follow patients throughout their time in hospital for surgery, reviewing their medical records and recording any clinical outcome. In hospital, all patients will have troponin measured postoperatively, and then on the 1st, 2nd, and 3rd day after surgery or until discharge, whichever comes first. Data on ischemic symptoms/signs will be collected, and an ECG will be

performed if an elevated troponin measurement is detected. Data on any other troponin measurement that will be undertaken in any study participant within 28 days from surgery will be also collected and will be assessed upon the study definition for MINS. In hospital, study personnel will administer the 3D-CAM twice a day, during the first 3 days after surgery or until discharge, whatever comes first. We will use the CAM-ICU while the patients are in the Post-Anesthesia Care Unit (PACU) or if sent to ICU.

A follow-up study visit will be done at 28 days, 6 months, and 12 months after surgery. Efforts will be made to perform such study visits in concomitance with clinical follow-ups. Frailty assessments will be repeated at 28 days. WHODAS 2.0 will be administered at 28 days, 6 months and 12 months, in-person or over the phone, by research personnel blinded from the frailty assessments. MoCA will be administered at 6 and 12 months (in-person or through videoconference). Study personnel will also collect clinical outcome data through the study follow-ups.

We will also assess physicians' and patients' acceptability of frailty assessments (Appendix III).

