## **6. STATISTICAL ANALYSES**

### **6.1 Primary Analysis**

The primary analysis will compare the performance of preoperative frailty assessment based on the FP and perioperative cardiovascular risk assessment based on the combination of preoperative RCRI, age and occurrence of MINS, in predicting the composite of all-cause death or new disability at 6 months after surgery. We will assess the association of FP and of RCRI+age+MINS with the primary outcome using logistic regression models. We will perform one logistic regression model including frailty as predictor, and one logistic regression model including the baseline RCRI+age+MINS as predictors. For each model we will then calculate the c-statistics (corresponding to the AUROC) and compare them using a non-parametric approach. We will include in the primary analysis only study participants who are alive at 28 days after surgery. We expect this will exclude from the primary analysis a very small proportion of patients initially enrolled in the study (i.e.,  $\leq 2\%$ ). We will initially exclude from the primary analysis those patients for whom postoperative troponin measurement was

not performed (for reasons other than death); as a sensitivity analysis, these patients will be then included and considered as not having MINS. For the primary analysis we will not include other covariates in the regression models. We will secondarily include the type of gynecological diagnosis/indication (based on our inclusion criteria) as covariate and as effect modifier.

As part of our secondary objectives, we will also evaluate the utility of frailty *when added* to the RCRI+age+MINS as predictors by calculating the net absolute reclassification improvement.

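### Separating WHODAS 2.0 staff from the frailty assessors does not blind them to RCRI, and nothing masks them to MINS, so the disability component is masked to one predictor but not to its comparator

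*Protocol*

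**What the plan says.** The primary outcome is all-cause death or new disability at 6 months. Disability is measured with the 12-item WHODAS 2.0, a patient-reported instrument that staff administer (sections 4.1 and 5.1).

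Section 4.5 sets out to limit how far knowledge of frailty status influences the disability evaluation. Its one measure is that "WHODAS 2.0 will be administered by different study personnel from those who administered the frailty assessments". It then draws a conclusion about a different variable: "In this way, they will be able to be blinded to the patient RCRI".

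Section 5.1 states the follow-up rule as administration "in-person or over the phone, by research personnel blinded from the frailty assessments". It mentions neither RCRI nor MINS.

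The primary analysis (6.1) sets a frailty model against "one logistic regression model including the baseline RCRI+age+MINS as predictors" and compares the two c-statistics on the same outcome.

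**The concern.** The inference in 4.5 is a non sequitur. Keeping the WHODAS 2.0 interviewer away from the grip test, the walking test and the frailty questions does nothing to hide cardiac history, creatinine, insulin use or type of surgery. MINS is left out of the blinding rule altogether.

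The primary question is a head-to-head comparison of two predictors on one shared outcome. The protocol itself accepts that an interviewer who knows a predictor might rate disability differently, yet it acts on this for only one of the two. If that influence exists, it can operate through the comparator but not through frailty, and it then enters the AUC difference under test. Analysis cannot repair this afterwards, because who may know what when the outcome is taken is settled by conduct.

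**Working it through.** The plan gives no figure on this point, so there is none to reproduce. The check is of the text, followed by a hypothetical illustration of size.

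**Where each predictor comes from, and what masks it**

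- Frailty Phenotype and CFS (3.1.1, 3.1.2): physical tests, questions and clinical judgement. Masked by the staff separation in 4.5 and by 5.1.
- RCRI (3.1.4): past medical history and type of surgery. Section 4.5 asserts that blinding is possible, but no procedure secures it. Section 5.1 is silent.
- Age: part of the comparator, not mentioned in either section, and hardly maskable from an interviewer.
- MINS (3.1.5): in-hospital troponins and any others within 28 days. Not mentioned in 4.5 or in the blinding clause of 5.1.

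The only other blinding statement is in 4.4. It covers the adjudicators of MINS and MI, and blinds them to treatment allocation, which a cohort study does not have. It says nothing about WHODAS 2.0 staff.

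**Could an interviewer learn RCRI or MINS?** Section 5.1 says: "Study personnel will follow patients throughout their time in hospital for surgery, reviewing their medical records and recording any clinical outcome". The Study Summary says: "Study personnel will evaluate all study outcomes at each follow-up visit". Figure 2 places WHODAS 2.0 and clinical outcomes at the same 28-day, 6-month and 1-year visits. These lines do not say that one person does both tasks, but nothing prevents it or restricts access to the forms.

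**Why the omission of MINS matters.** Under 3.1.5 a patient is high risk on the comparator only if RCRI+age is high *and* MINS occurs; everyone without MINS is low risk. MINS is therefore necessary for being exposed, and it is the component that 4.5 never names.

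**If RCRI in 4.5 is a slip for frailty status**, the sentence becomes consistent with its aim and with 5.1. The comparator then has no blinding statement at all, so the imbalance remains.

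**Illustration of size**

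From the protocol: 20% events, comparator AUC 0.55 to 0.60 (2.3), planned difference 0.13 and 250 patients (Appendix I). Assumed here, with no basis in the protocol: a share *e* = 10 to 25% of patients in the high-risk category, and a share *d* = 5 to 20% of exposed patients without an event recorded as newly disabled because the interviewer knew their status. The frailty AUC is held fixed.

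For a binary predictor, AUC = (sensitivity + specificity)/2 = 0.5 + (s − f)/2, where s is sensitivity and f the false-positive rate. So s − f = 2·AUC − 1, and 0.2·s + 0.8·f = *e* gives f = *e* − 0.2·(2·AUC − 1).

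After relabelling:

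- s′ = (0.2·s + 0.8·f·*d*) / (0.2 + 0.8·f·*d*)
- f′ = 0.8·f·(1 − *d*) / (0.8 − 0.8·f·*d*)

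Middle case, AUC 0.55, *e* = 0.15, *d* = 0.10:

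- f = 0.15 − 0.02 = 0.13; s = 0.23
- relabelled share = 0.8 × 0.13 × 0.10 = 0.0104, or 0.0104 × 250 = 2.6 patients
- s′ = 0.0564/0.2104 = 0.268; f′ = 0.0936/0.7896 = 0.119
- new AUC = 0.5 + (0.268 − 0.119)/2 = 0.575, a rise of 0.025

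Ends of the range:

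- Smallest (AUC 0.60, *e* = 0.10, *d* = 0.05): f = 0.06, 0.8 × 0.06 × 0.05 × 250 = 0.6 patients, AUC 0.606, a rise of 0.006.
- Largest (AUC 0.55, *e* = 0.25, *d* = 0.20): f = 0.23, 0.8 × 0.23 × 0.20 × 250 = 9.2 patients, AUC 0.621, a rise of 0.071.

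This shows that few patients would be needed to move the comparator AUC noticeably. It does not show that any would be misrated.

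**The case against.** The case for leaving this alone, or treating it as a one-word correction, is substantial.

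- *RCRI may be a slip, and the sentence is only permissive.* Both are fair. It is more accurate to say that no procedure secures the blinding than that it does not exist. Neither point gives the comparator any protection.
- *The rest argues from silence.* The text says only study personnel, and the Manual of Operations promised in 9.1 may assign roles. This stands as far as practice goes: a reader might infer that the interviewer will know MINS, and the protocol does not say so. But a manual that cannot be seen does not correct a mistaken statement in the protocol.
- *The mechanism is weak.* The patient supplies the answers, the primary reading is six months after surgery, MINS can be symptomless (1.2.2), and the MINS used in analysis is the adjudicated one (4.4). Frailty overlaps the content of WHODAS 2.0 far more directly, so masking it first is defensible. All of this stands and is why the effect is probably modest.
- *Death cannot be altered by an interviewer.* This stands. A reader might infer that the whole primary outcome is unprotected, or that it is mostly a questionnaire result. The protocol gives no split between death and disability. Section 1.2.2 reports 14% one-year mortality in comparable women without MINS who did not meet the RCRI+age criteria, so deaths may be a sizeable share of the expected 20%.
- *The size is assumption only.* This stands. Nothing in the protocol supports a particular exposed share or rate of misrating.

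**Conclusion.** The point holds in limited form. Section 4.5 claims a protection that its procedure does not deliver, and neither 4.5 nor 5.1 masks WHODAS 2.0 staff to MINS. The disability component of the primary outcome is therefore masked to frailty and not to RCRI+age+MINS, which could bias the AUC comparison. This conclusion rests on the text alone and needs no assumed numbers.

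The range of 0.006 to 0.07 against 0.13 is a sensitivity range, not a forecast. It rests on the assumed exposed share and misrating rate, a binary comparator and an unchanged frailty AUC. It is also tempting to conclude that the bias must favour the comparator. That follows only if knowing about MINS raises recorded disability, in which case the frailty advantage shrinks and power is lost. If knowledge led interviewers to discount disability, the advantage would grow. The documents do not settle which.

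**What to change.** Replace the last sentence of 4.5 and align 5.1 along these lines:

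*At the 28-day, 6-month and 1-year visits, staff administering WHODAS 2.0 have no access to that patient's FP, CFS, RCRI and troponin/MINS forms. WHODAS 2.0 is completed before any clinical-outcome question at the visit, by telephone where useful. Where existing staffing permits, the person administering it is not the one who recorded that patient's troponin/MINS data.*

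Where a site cannot arrange this last separation, the protocol should state that its WHODAS 2.0 staff are not blinded to RCRI/MINS and drop the claim of blinding.

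The cost is protocol wording, form-access settings and visit order, which the sites must manage. Section 4.5 already requires a second person for WHODAS 2.0, and 5.1 already allows the telephone. Barring that person from all history-taking and in-hospital follow-up would go further but might need extra staff at small sites, so it is not asked for here.

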## **5. FOLLOW UP**

### **5.1 Overall study**

Figure 2 shows the study participant timeline.

At baseline (i.e. before surgery, or before NACT for some cases), trained research personnel will collect relevant data about participant demographics, clinical and social history; will administer the WHODAS 2.0 questionnaire and the MoCA; and will assess for frailty. A trained clinical research assistant will measure frailty, first based on the CFS, and then administering the FP tests/questions. In patients undergoing NACT, the study personnel will repeat the frailty, WHODAS 2.0, and MoCA assessments before surgery, after the NACT is deemed to be terminated.

Study personnel will follow patients throughout their time in hospital for surgery, reviewing their medical records and recording any clinical outcome. In hospital, all patients will have troponin measured postoperatively, and then on the 1st, 2nd, and 3rd day after surgery or until discharge, whichever comes first. Data on ischemic symptoms/signs will be collected, and an ECG will be

performed if an elevated troponin measurement is detected. Data on any other troponin measurement that will be undertaken in any study participant within 28 days from surgery will be also collected and will be assessed upon the study definition for MINS. In hospital, study personnel will administer the 3D-CAM twice a day, during the first 3 days after surgery or until discharge, whatever comes first. We will use the CAM-ICU while the patients are in the Post-Anesthesia Care Unit (PACU) or if sent to ICU.

A follow-up study visit will be done at 28 days, 6 months, and 12 months after surgery. Efforts will be made to perform such study visits in concomitance with clinical follow-ups. Frailty assessments will be repeated at 28 days. WHODAS 2.0 will be administered at 28 days, 6 months and 12 months, in-person or over the phone, by research personnel blinded from the frailty assessments. MoCA will be administered at 6 and 12 months (in-person or through videoconference). Study personnel will also collect clinical outcome data through the study follow-ups.

We will also assess physicians' and patients' acceptability of frailty assessments (Appendix III).

A patient engagement component will also be included. Patient engagement will be refined throughout the study with input from the patient engagement members according to Patient Engagement Integrated Knowledge Translation Committee Charter. At least two community members will be invited to join to create a viable patient engagement and integrated knowledge translation plan that will meet instrumental and strategic targets as defined by the committee.

